### Management of Adverse Events

All adverse events that occurred during the trial must be faithfully recorded. Researchers should give targeted treatment and follow-up for adverse events until the symptoms disappear or become stable.

For serious adverse events in the clinical trial, the investigator should immediately take appropriate treatment measures to the subject, and at the same time report to the medical device clinical trial management department in writing and notify the sponsor in writing through the department. The medical device clinical trial management department should report to the relevant ethics committee, the Food and Drug Administration and the health and family planning department of the province, autonomous region, and municipality in writing within 24 h. For deaths, clinical trial institutions and researchers should provide all necessary information to the ethics committee and sponsors.

When device defect occurs, replace it with the same device or take conventional treatment. For device defects that cause or may cause serious adverse events, the sponsor should report to the registered FDA and the health and family planning authority at the same level within 5 working days. At the same time, it should notify other clinical trial institutions and researchers participating in the trial and timely informs the ethics committee of the clinical trial institution through the medical device clinical trials management department.

### Randomization

Immediately after DSA and prior to mechanical thrombectomy, 192 patients are randomly allocated in a one-to-one ratio to either experimental or control group using an Internet-based Central Random System (IWRS). When grouping the patients, stratification will be performed to control key indicators by the clinical trial center and the baseline NIHSS score (divided by NIHSS score ≤ 17 points or > 17 points) (2).

### Reduction and Avoidance of Bias

The following measures have been taken to reduce and avoid bias:

NIHSS and mRS score were assessed by physician independent of the operator in each clinical trial center. The images are reviewed by the core laboratory to assess time of successful recanalization and the grade of the blood flow of the target vessel before and after the operation. When the result is different from the clinician's judgment, the core laboratory result shall prevail.

Sponsors, clinical trial supervisors, and researchers took corresponding measures to reduce the bias on results during the trial, including training for investigators before the start of the study to make sure they are familiar with research procedure and device operation, selecting skilled and experienced surgeons who has completed more than 30 mechanical thrombectomy operations, ensuring that the experimental protocol is strictly followed, following the requirements of relevant treatment guidelines, and data verification after the completion of clinical trials.

### Monitoring Plan

The sponsor should select qualified supervisors to perform supervisory duties on all participating institutions. Before the trial, supervisors should confirm the clinical trial institution has the appropriate conditions including the staffing and training meeting the requirements, well-equipped laboratory, good working condition, sufficient number of subjects, and the researchers are familiar with the test requirements. They should also supervise whether the clinical trial institutions and researchers comply with relevant regulations, and supervise medical device samples and related equipment during the trial. And supervisors must confirm that each subject signs an informed consent before participating in the clinical trial and all case report forms are filled correctly and consistent with the original data, and ensure that all clinical trial related documents received by investigators are new versions. Detailed information must be recorded for patients who withdrew from the experiment, don't follow the informed consent form, and are not followed up completely, as well as all adverse events, complications, and other device defects.

### Ethical Considerations and Informed Consent

This clinical trial comply with the Declaration of Helsinki, Medical Device Clinical Trial Quality Management Regulations and Chinese relevant laws and regulations. Before the start of the trial, the protocol must be approved by the ethics committee of each research center. The investigators should provide the subjects or their guardians complete information about the trial and should not compel or induce subjects to participate in the trial in improper ways. If the subjects have a disturbance of consciousness or have a difficulty in understanding language, the investigator should fully explain the details of the clinical trial to their guardian, and the guardian and investigators shall sign their name and date on the written informed consent prior to enrollment and keep it in the research files.

### Sample Size

The calculation of the sample size is based on the successful recanalization rate evaluated during the operation. Based on the results of the North American Solitaire post-marketing study (18), the meta-analysis of thrombectomy devices (2), and a multi-center registered clinical trial (EAST) led by [name] of Tiantan Hospital, it is expected that the test group can reach the same efficiency when the sponsor and clinicians assumed the rate of successful recanalization after treatment was about 90% in the control group. Eventually, a total of 192 patients were enrolled according to calculation based on statistical principles, 96 cases in each group with a 12.5% non-inferiority margin, a 5% significance level (two-tailed), an 80% statistical power and a 5% dropout rate.

### Statistical Analysis

For descriptive analysis, enumeration data will be expressed by frequency and composition ratio, and the measurement data will be expressed by the mean, standard deviation, maximum, minimum, median, 25th and 75th quantile.

For baseline demographics, all date will be analyzed based on full analysis set. Continuous calibration Chi-square tests or Fisher's exact tests will be used for comparison of enumeration data between groups. Group *t-*test will be used for comparison of normally distributed measurement data between groups, and Wilcoxon Rank Sum test for non-normally distributed measurement data.

For the primary outcome, the successful recanalization rate of blood vessels, the CMH chi-square analysis with adjusted center effect will be used for comparison between groups based on full analysis set and per protocol set. In addition to the success rate, the difference in the success rate between the experimental group and the control group and the 95% confidence interval with the lower bound greater than −12.5% will be also estimated.

Other efficacy indicators comparation between groups will be the same as the baseline analysis. The paired *t-*test will be used for the intra-group comparison of normally distributed measurement data and the Wilcoxon Sign Rank test for the intra-group comparison of non-normally distributed measurement data.

For safety evaluation, the number and proportion will be used to describe cases that were normal before treatment and abnormal after treatment in the full analysis set. Adverse events will be described by number and incidence, and this incidence will be tested by continuous calibration Chi-square tests or Fisher's exact tests. At the same time, the specific manifestations and extent of all adverse events in each group and their relationship with the research products will be described in detail.

For missing data, only the missing primary endpoint indicators will be carried forward during analysis, while other indicators will be not. Incorrect and unreasonable data will be checked by the electronic data capture (Electronic Data Capture, EDC) system and the question will be answered by the researcher before statistical analysis. For patients withdrawing from the trial, the information will still be included in the final statistical analysis.

All data will be analyzed using SAS9.4 software and all statistical analysis will be performed at the two-sided 0.05 significance level (except for special instructions).

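### Between-arm tests of NIHSS and mRS ignore the baseline NIHSS used to stratify randomisation, so they are valid but conservative; the added within-arm tests do not compare the devices

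*Protocol article*

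**What the plan says.** The Statistical Analysis section gives the baseline tests first. For categorical data: "Continuous calibration Chi-square tests or Fisher's exact tests will be used for comparison of enumeration data between groups". For continuous data it names a two-sample t-test under normality and otherwise the "Wilcoxon Rank Sum test for non-normally distributed measurement data". It then carries these tests over to every non-primary efficacy endpoint: "Other efficacy indicators comparation between groups will be the same as the baseline analysis". None of them takes a covariate or a stratum.

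Within-arm testing follows. The paired t-test "will be used for the intra-group comparison of normally distributed measurement data", with the "Wilcoxon Sign Rank test for the intra-group comparison of non-normally distributed measurement data" as the alternative.

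For the primary endpoint there is some adjustment, for centre only: "the CMH chi-square analysis with adjusted center effect will be used for comparison between groups".

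Randomisation is stratified on two factors, "the clinical trial center and the baseline NIHSS score", the latter cut at 17. The Discussion gives the reason: to keep preoperative NIHSS and centre from influencing the results. Table 1 has NIHSS recorded before the operation, at 24 h and at 7 days. The inclusion criteria allow baseline scores from 6 to 29. Endpoint Measurement lists 7-day NIHSS, 90-day mRS and mRS 0–2 as secondary efficacy endpoints; the Abstract adds 24 h NIHSS.

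**The concern.** The design treats baseline NIHSS as important enough to control at randomisation, yet no between-arm analysis uses it. When allocation is balanced on a prognostic factor and the analysis ignores that factor, the usual standard error is too large: it still counts variation that the design has removed. The test then rejects less often than its nominal level and the interval is wider than the data warrant.

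That matters somewhat more here than in a superiority trial. The Discussion describes the purpose as showing similar safety and efficacy. An underpowered difference test on the clinical outcomes makes a non-significant result more likely, and such a result is easily read as similarity. The affected endpoints are the patient-level clinical measures of efficacy; the primary endpoint is angiographic.

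The within-arm tests are a separate weakness. Both arms undergo thrombectomy, so both may change from baseline whichever retriever is better. For mRS, the only baseline that the text defines is the prestroke score, so pairing it with day 90 contrasts prestroke with post-stroke disability. That is no comparison of devices either.

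**Working it through.** **1. The plan's own figure.** Inputs from Sample Size: 90% in both arms, margin 12.5%, two-sided 5%, power 80%, dropout 5%.

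n = (1.960 + 0.842)² × 2 × 0.90 × 0.10 / 0.125² = 7.849 × 0.18 / 0.015625 = 90.4, so 91 per arm. With dropout, 91 / 0.95 = 95.8, so 96 per arm and 192 in total. The stated figure reproduces. It rests on recanalization alone; no calculation is given for NIHSS or mRS. Steps 2 to 4 use 91 evaluable patients per arm.

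**2. Nominal variance.** Adjusting a continuous outcome for a baseline score with correlation r multiplies the error variance by 1 − r², and the interval width by √(1 − r²). The documents do not give r; 0.3 to 0.7 is assumed.

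**3. Actual behaviour under stratified allocation.** A simulation of 4,000 runs per setting used 182 patients, baseline NIHSS drawn around 16.5 (SD 5.5) and limited to 6–29, blocks of 4 within ≤17 and >17, and a normal outcome with unit variance. Centre was not modelled. Power is for an assumed standardised difference of 0.4.

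| r | 1 − r² | Interval width ratio | SD of estimate, t-test | SD of estimate, ANCOVA | Actual variance ratio | Type I error, t-test | Type I error, ANCOVA | Power, t-test | Power, ANCOVA |
|---|---|---|---|---|---|---|---|---|---|
| 0.3 | 0.91 | 0.954 | 0.1442 | 0.1423 | 0.97 | 4.72% | 4.88% | 0.77 | 0.80 |
| 0.5 | 0.75 | 0.866 | 0.1339 | 0.1265 | 0.89 | 3.22% | 4.45% | 0.79 | 0.87 |
| 0.7 | 0.51 | 0.714 | 0.1220 | 0.1062 | 0.76 | 1.40% | 4.75% | 0.81 | 0.97 |

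The actual variance ratio is the squared ratio of the two SDs, for example (0.1265 / 0.1339)² = 0.89. The Monte Carlo standard error of a 5% rejection rate is √(0.05 × 0.95 / 4000) = 0.34 percentage points. The t-test figure at r = 0.3 therefore cannot be told from 5%; those at 0.5 and 0.7 are clearly below it.

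**4. Cross-check at r = 0.5.** The t-test assumes a standard error of √(2/91) = 0.148, but the estimate actually varies with SD 0.134. The ratio is 0.1339 / 0.1482 = 0.903, so the critical value of 1.96 acts like 1.96 / 0.903 = 2.17. Its two-sided tail is about 3.0%, in line with the simulated 3.2%.

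**5. Within-arm tests.** Assume identical devices, a change SD of 8 points and 91 per arm. The standard error of the mean change is 8 / √91 = 0.839.
- True mean change 5 points: 5 / 0.839 − 1.96 = 4.0, so each arm is significant practically always.
- True mean change 2 points: 2 / 0.839 − 1.96 = 0.425, so each arm is significant with probability 0.665. Exactly one arm is significant with probability 2 × 0.665 × 0.335 = 0.446.

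So two identical devices would look different on within-arm p-values in about 45% of such trials, and with a larger common change both arms would be significant without informing the comparison.

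**The case against.** The strongest reply is that unadjusted tests of randomised arms are a legitimate choice for secondary endpoints, that the article condenses a fuller protocol, and that adjusted supporting models are often left to an analysis plan. The first part stands as far as validity goes: nothing here makes a false claim of a device difference more likely. The second part carries less weight, because the article does not leave the method open. It names the tests.

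Several stronger readings are tempting, and the documents do not support them.

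- A reader might infer that the unadjusted between-arm comparisons are biased or uninformative. They are unbiased; only the within-arm tests fail to address the device difference.
- A reader might take 1 − r² as the gain in true precision, so that at r = 0.5 the 96 patients per arm would be worth 96 / 0.75 = 128. That would hold for unstratified allocation. With stratification at 17 the actual variance ratio is about 0.89, or 96 / 0.89 ≈ 108 per arm. The 25% describes the reported standard error and interval, not the spread of the estimate.
- A reader might infer that the protocol means to claim equal efficacy from within-arm changes. No section says so; it is a risk of misreading.
- A reader might say that baseline NIHSS enters no efficacy analysis at all. The paired tests on NIHSS do use it. What is missing is its use in any between-arm comparison.
- A reader might extend the figures to mRS and mRS 0–2. They apply to a continuous NIHSS analysis only.

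**Conclusion.** The point holds in a limited form. The plan fixes between-arm tests that ignore a randomisation stratum recorded in every patient. The result is conservative inference on the secondary clinical endpoints: little loss if baseline NIHSS correlates 0.3 with outcome, a noticeable one at 0.5 (type I error about 3.2%, power 0.79 against 0.87), and a substantial one at 0.7 (1.4%, 0.81 against 0.97). The reduction in the true variance of the estimate is about a tenth at 0.5.

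These sizes rest on an assumed correlation, a normal outcome, an assumed block size and a simulation without centre. With more than 10 centres there are at least 11 × 2 = 22 strata, averaging no more than 192 / 22 = 8.7 patients. Balance on NIHSS could be looser than simulated if blocks stay incomplete; the t-test would then be less conservative and the real gain from adjustment larger.

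The primary non-inferiority conclusion and the 192-patient sample size do not depend on any of this. The correction is worth making because the data are already there, but it is not critical to the trial.

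**What to change.** Replace the sentence that carries the baseline tests over to the other efficacy endpoints:

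- Follow-up NIHSS: ANCOVA with baseline NIHSS as a continuous covariate, giving a between-arm difference in points.
- 90-day mRS: ordinal regression with baseline NIHSS.
- mRS 0–2: logistic regression with baseline NIHSS, reported as a standardised risk difference.

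Include centre in each model, with small centres pooled or centre fitted as a random effect, since strata will be sparse. Report each between-arm estimate with its 95% confidence interval, and keep the unadjusted tests as sensitivity analyses. Drop the within-arm tests, or present change from baseline by arm as description without p-values. How deaths enter the NIHSS analysis is a separate choice of estimand and need not be settled by this change.

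The cost is analysis wording and some programming. The covariates are already collected, and no visit, endpoint or patient number changes.

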### Date Management

The data management will be in the charge of the Medical Statistics Department of the National Cardiovascular Disease Center, and the data collection will be performed by them using EDC system. Researchers are responsible for the quality of the data entry, and should ensure the authenticity and completeness of the data. Data verification is completed by both the EDC system and the data administrator. The modification and locking of data need to be approved by the sponsor, the person in charge of data management, and the person in charge of statistics.

## Discussion

Stent retriever has recently been widely used for thrombectomy, and has been reported to be associated with faster reperfusion and higher rate of successful recanalization in endovascular treatment of intracranial LVO (19). However, the research and development of domestic stent retrievers is relatively slow and few devices have been verified by clinical trials (15), which greatly hinders the progress of endovascular treatment in China. The purpose of this trial is to verify whether the new thrombectomy device-Skyflow has similar safety and efficacy compared with Solitaire FR in the treatment of acute LVO.

Compared with other stent retriever, the device-Skyflow has some unique structural features (15, 20, 21). The double helix structure makes stent have excellent flexibility and adhesion, which improve the thrombus removal rate, while avoid excessive damage for intracranial blood vessels. Partial large mesh design and the wall thickness greater than the rod width can effectively embed and remove the thrombus. Full development design helps the doctor to determine the position and length of the stent and its unfolding shape which can improve the success rate of the operation. The pushing wire of the thrombectomy device is made of nickel-titanium material, and the distal end is designed as a variable-diameter structure coiled with platinum alloy coil, which improves the pushability and visualization of the product. And the device has different models and specifications, which can meet the requirements of occluded vessel with different diameters. All these features provide theoretical basis for the safety and efficacy of the test product. But relative to the reel overlap design and multi-target combination with thrombus of solitaire FR, the Skyflow has a weaker cutting and grasping ability for thrombus. In addition, compared to solitaire FR, the delivering catheter of Skyflow device is larger, which may make it difficult to pass the Atherosclerotic stenosis.

The Solitaire FR is a representative of stent retriever and the technology is mature. The main structure, action principle, treatment method, indications, etc. are similar to the test product (20). Therefore, it is reasonable to choose Solitaire FR device as a control product in our trial. In addition, this trial has strict inclusion and exclusion criteria. DSA is used to identify the occlusion site, and CT or MRI to exclude patients with preoperative intracranial hemorrhage and large core infarct. And the trial adopted a stratified random approach to avoid the influence on the results of preoperative NIHSS score and different research centers. A series of other measures have also been taken to ensure the quality of research, including the supervision of the experimental equipment of clinical trial institutions and relevant training for the investigators, quality control and monitoring, and data management and check after the research etc. These can make the trial results more convincing. But this is a single-blind clinical trial. The researchers cannot be blinded due to the difference of appearance between the test device and the control device, which can cause an impact on the trial results.

In conclusion, results of this trial will provide information on the safety and efficacy of Skyflow stent retriever. The success of this trial will provide a new option for the treatment for patients of AIS with LVO in China.

## Ethics Statement

The studies involving human participants were reviewed and approved by Ethics Committee of Drugs (Devices) Clinical Experiment in Henan provincial People's Hospital and other research centers participating in the clinical trial. The patients/participants provided their written informed consent to participate in this study.
